## Abstract

**Background:**

Cancer survivors are often left on their own to deal with the challenges of resuming work during or after cancer treatment, mainly due to unclear agreements between stakeholders responsible for occupational rehabilitation. Social inequality exists in cancer risk, survival probability and continues with regard to the chance of being able to return to work.

The **aim** is to apply an early, individually tailored occupational rehabilitation intervention to cancer survivors in two municipalities parallel with cancer treatment focusing on enhancing readiness for return to work.

**Methods/Design:**

In a controlled trial municipal job consultants use acceptance and commitment therapy dialogue and individual-placement-and-support-inspired tools with cancer survivors to engage them in behaviour changes toward readiness for return to work. The workplace is involved in the return to work process.

Patients referred to surgery, radiotherapy or chemotherapy at the Oncology Department, Aarhus University Hospital, Denmark for the diagnoses; breast, colon-rectal, head and neck, thyroid gland, testicular, ovarian or cervix cancer are eligible for the study. Patients must be residents in the municipalities of Silkeborg or Randers, 18–60 years of age and have a permanent or temporary employment (with at least 6 months left of their contract) at inclusion. Patients, for whom the treating physician considers occupational rehabilitation to be unethical, or who are not reading or talking Danish are excluded. The control group has identical inclusion and exclusion criteria except for municipality of residence.

Return to work is the primary outcome and is indentified in a social transfer payment register. Effect is assessed as relative cumulative incidences within 52 weeks and will be analysed in generalised linear regression models using the pseudo values method. As a secondary outcome; co-morbidity and socio-economic status is analysed as effect modifiers of the intervention effect on return to work.

**Discussion:**

The innovative element of this intervention is the timing of the occupational rehabilitation which is much earlier initiated than usual and the active involvement of the workplace. We anticipate that vulnerable cancer survivors will benefit from this approach and reduce the effects of social inequality on workability.

**Trial registration:**

Current Controlled Trials ISRCTN50753764. Registered August 21^st^, 2014.

## Background

### Cancer and return to work

Cancer prevalence has increased worldwide in recent years due to improvements in diagnostic procedures and treatment [1]. Approximately 40 % of new cancers are found in the working population [2], of whom many are motivated for and expect to return to work (RTW) [3], as RTW constitutes “normalcy”, has impact on quality of life and economic independence [4, 5]. However, the cancer disease and the treatment still increases the risk of early withdrawal from the labour market [6, 7]. Even though work is perceived as an important factor in quality of life [8, 9], for some cancer survivors work participation may be deprioritised by other ways of active participation in society [10]. Therefore knowledge on how cancer survivors value their work and how this affects the RTW process is needed. Among cancer survivors who do RTW some may face both health-related and work-related difficulties leading to reduced workability and recurrence of sick leave [11], which further increases the risk of prematurely exit from the labour market [12]. Some consistency exists in the literature about which factors are associated with RTW despite adverse side-effects from cancer treatment [13]. However, often cancer patients are left on their own to deal with these challenges [11, 14, 15, 10]; partly due to unclear agreements between stakeholders responsible for occupational rehabilitation [10, 16] and partly due to reluctance and fear of articulating work and RTW to a cancer survivor [17].

Research on RTW in cancer survivors has in recent years increased, partly because survival rates have increased [18, 19], and because patients with advanced, incurable disease are able to perform some kind of work, and will often prefer to stay on the labour marked as long as possible. Nevertheless, there still is a need for rigorous studies applying a randomised controlled trial design, with thorough information on intervention components and data reporting [19]. Due to the inconsistent conclusions drawn from the existing RTW studies in cancer survivors; evidence from research conducted on musculoskeletal and/or mental-related sickness absentees can give insights into effective RTW interventions in general and guide researchers in putting hypotheses forward on which elements cancer-oriented RTW interventions may contain. Thus, the provision of occupational rehabilitation to cancer survivors that consists of a combination of general and cancer specific intervention elements may prove to be an effective approach.

Some evidence supports that RTW interventions targeted musculoskeletal-related [20] or depressed absentees [21] are more effective when they address the workplace than interventions not targeting the workplace. Thus, in the planning of the present study it was crucial to incorporate involvement of the workplace as one of the key elements in the intervention. In a cancer setting it has been shown that employer and colleague support as well as work accommodation increases the RTW rate and reduces the likelihood of cancer-related work impairments after RTW [13].

Problem-solving-therapy interventions towards employees sick-listed due to adjustment disorders enhanced partial RTW compared to a non-guideline based care [22]. Cancer survivors may also display adjustment disorders due to difficulties in coping with having a cancer diagnosis along with expectations from relatives and friends, workplace and health care professionals in the RTW process. Fear of cancer recurrence may lead to fear avoidance behaviour, which limits participation in life - including work [23, 24]. Therefore, the identification of cancer survivor-experienced barriers regarding RTW and assistance in barrier modification were important elements that the present intervention should include.

Feuerstein et al. developed the Work and Cancer Model based on an extensive review of the literature [25]. A variety of factors coexists and may act both as facilitators and inhibitors of RTW among cancer survivors; individual characteristics, health and well-being, symptoms, function, work demands, work environment and finally structural factors [25]. There seems to be agreement in the literature that RTW-interventions in general should target the multi-dimensional factors that are associated with sickness absence and that seems also to be true in a cancer specific context. This perspective is in part substantiated in the Cochrane review by de Boer et al. on RTW interventions to cancer survivors. Although the studies had low quality it was concluded that one-dimensional interventions, i.e. psychological, physical or medical interventions did not improve RTW compared to care as usual, whereas a moderate quality evidence was found for a multidisciplinary approach (involving physical, psychological and vocational elements) compared to care as usual [18].

Cancer survivors in low socioeconomic groups may in particular experience the RTW-process difficult and tend to be at risk of recurrent sickness absence, unemployment or permanent withdrawal from the labour market [7, 26, 27]. It is not clear which role socioeconomic status plays on cancer survivors’ RTW-process, but unfavourable work conditions characteristic for low income and low-level educational jobs may explain some of this inequality [28]. Therefore work accommodations and supervisor support may be of particular importance in occupational rehabilitation in cancer survivors [3, 10, 29] to help cancer survivors overcome the imbalance between health and work demands.

Despite improved long-term survival rates for cancer patients, survivorship does not mean living without health complaints, but rather living with a chronic disease [30]. Cancer survivors do have an increased risk of recurrent cancers along with co-morbidities like cardiovascular disease, diabetes, osteoporoses etc. [31]. This further increases the risk for reductions in workability and calls for collaboration between the occupational rehabilitation stakeholders to enhance the chance of sustainable RTW.

### The Danish healthcare system

Permanent residents in Denmark pay approximately 40-50 % taxes of their income, by which almost all examinations and treatments within the Danish healthcare system are free of charge. The Danish Health and Medicines Authority is responsible for the organizational and clinical standards for the diagnostics and treatment for all cancer types, i.e. integrated cancer pathways [16]. The objective of the pathways is to reduce referral time, obtain faster diagnosing and early onset of treatment. To accomplish these general goals the pathways are operationalised in several Disease Management Programmes for Cancer of which one defines Rehabilitation and Palliation in Cancer [16]. The specific aim of cancer rehabilitation is, besides optimizing the patient's physical, psychological and social functioning while countering the limitations imposed by the side effects of cancer treatments and/or co-morbid conditions, also to offer occupational and vocational rehabilitation [32]. Few studies have been conducted on occupational rehabilitation offered parallel to cancer treatment at the hospital [33, 34], however more studies are ongoing/in preparation [35–37]. Thus, knowledge is scarce on whether occupational rehabilitation applied early and parallel to cancer treatment facilitates the RTW-process for cancer survivors. To our knowledge, no studies have been conducted in a Danish setting or in other Nordic countries, which has similar tax-financed health care systems as Denmark.

### Sickness absence management in Denmark

According to the Danish Sickness Benefit Act [38], the municipal job centres are responsible for paying sickness benefits and initiating occupational/vocational rehabilitation to help sick-listed persons to RTW.

All employed, self-employed, temporarily employed and unemployed persons fulfilling the criteria of previous employment (minimum 74 h within a period of 8 weeks) are eligible for sickness benefits.

According to law, the employer pays sickness benefits during the first 4 weeks, afterwards the municipality refunds the employer’s wage expenses for a maximum period.

The regulations for sickness benefits have been subject to several changes [39] and continue to be so. When the study started the maximum period was 52 weeks within a period of 78 weeks. From July 2014 the maximum period in general was reduced to 26 weeks. However, extensions can be granted and for persons suffering from cancer the maximum period may be unlimited.

Medical certificates were not mandatory but could be requested by the municipal social security system and the employer. However, from January 2015 a medical certificate became obligatory after 8 weeks of sickness absence.

After the newest reform in 2014–15 the sickness beneficiaries are assigned into three categories: Category 1 includes persons who are likely to RTW within eight weeks without intervention. Category 2 includes persons who are unlikely to RTW within eight weeks unless activities facilitating RTW are initiated, i.e. coping-sessions and graded RTW. Category 3 includes persons who are unlikely to RTW within eight weeks unless multidisciplinary rehabilitation is implemented. This is planned by a municipal rehabilitation team within 12 weeks.

In accordance with the law sickness benefit officers are obliged to conduct regular follow-up interviews at least every four weeks with beneficiaries in category 2 and 3. Thus, municipal officers have been appointed the role as case managers, whereas employers have little responsibility for sickness absence management after they have had the first obligatory meeting with the employee after four weeks of sick-listing.

Most cancer survivors may be assigned in category 2, but in reality they are often spared the obligatory meetings with the social security officer and activities initiated by the job centre while receiving their treatment. This leads to a short time frame in which the cancer survivors are offered vocational/occupational rehabilitation; i.e. time between the end of treatment and the maximum period of sickness benefit reimbursement. Offering early occupational rehabilitation parallel to cancer treatment focusing on preparations for RTW and making arrangements together with the employer regarding work accommodations, graded RTW etc. should improve the RTW-process and reduce the recurrent sickness absence after RTW.

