### Participants

#### Intervention group

Cancer patients diagnosed with breast, colon-rectal, head and neck, thyroid gland, testicular, ovarian or cervix cancer referred to surgery, radiotherapy or chemotherapy at the Oncology Department at Aarhus University Hospital. Patients must be residents in the municipalities of Silkeborg or Randers, be at the age of 18–60 years and have a permanent or temporary employment (with at least 6 months left of their contract) at the inclusion date. Patients are eligible for participation whether they are still working or being on sick leave.

Patients, for whom the treating physician considers occupational rehabilitation to be unethical, or who are not reading or talking Danish are excluded.

Recruitment started in December 2013 and continues until the required sample size is obtained.

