#### Control group

The control group is defined by patients with identical inclusion and exclusion criteria as the intervention group except that they live in other municipalities than Silkeborg and Randers.

The control group is identified via the electronic patient records at the Aarhus University Hospital.

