### Intervention

#### Control group

Cancer survivors in the control group will receive the usual municipal sickness benefit management within their municipal of residence as described in the background.

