### Statistical analyses

#### Primary outcome

The cumulative incidence proportion (CIP) as a function of the number of follow-up weeks is estimated using the Kaplan-Meier curve. The relative cumulative incidence of RTW within 52 weeks will be analyzed in a generalised linear regression model using the pseudo values method [63, 64].

Entry time is defined as the end of cancer treatment (identified from the hospital records) and the end of follow-up is 52 weeks following entry time. The outcome variable RTW consists of two measures: an event indicator (yes or no) and the time until RTW is identified in the DREAM register [65] or end of follow-up / competing risks (*early retirement benefit, retirement pension or death*)/censored observations (*emigration*), whichever comes first.

Adjustments for gender, age, cancer diagnosis, time since diagnosis and Charlson’s co-morbidity index [58] are going to be carried out. Moreover, analyses of whether socio-economic status or Charlson’s co-morbidity index modifies the effect of the intervention on RTW will also be carried out.

The significance level is set at p < 0.05. The results will be shown as crude and adjusted relative cumulative incidences, i.e. risks (RR) and corresponding 95 % confidence intervals (95 % CI).

STATA version 13.1 will be used as statistical software.

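### Sickness-benefit law changed during recruitment, yet the plan neither ties controls to the intervention group's calendar window nor adjusts for calendar period; the likely bias is small and cheap to exclude.

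*Protocol article*

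**What the plan says.** **The law.** The Background section on sickness absence management in Denmark describes rules that changed while the study was recruiting. At the outset, "When the study started the maximum period was 52 weeks within a period of 78 weeks". Then: "From July 2014 the maximum period in general was reduced to 26 weeks". It adds a qualification: "However, extensions can be granted and for persons suffering from cancer the maximum period may be unlimited". A further change followed: "However, from January 2015 a medical certificate became obligatory after 8 weeks of sickness absence". The same section describes a 2014–15 reform that sorts beneficiaries into three categories with different follow-up.

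**The groups.** Under Participants, Intervention group: "Recruitment started in December 2013 and continues until the required sample size is obtained". Under Participants, Control group, controls have the same criteria apart from municipality, and "The control group is identified via the electronic patient records at the Aarhus University Hospital". No dates are attached. Under Intervention, Control group, these patients "will receive the usual municipal sickness benefit management", with a reference back to the Background description.

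**Outcome and model.** Return to work (RTW) means four consecutive weeks in the DREAM register with no transfer payment, or in a flexi job (Outcomes, Primary). Follow-up runs for 52 weeks from the end of cancer treatment. The model section lists "Adjustments for gender, age, cancer diagnosis, time since diagnosis" and the Charlson index as adjusters. Calendar time is not among them.

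**The concern.** The groups are not randomised, so nothing in the design guarantees that they are spread over calendar time in the same way. The comparator is a legal regime that moved during intake. The endpoint is read from payments under that regime, so a shorter benefit period could itself register as RTW when payment stops. If one group had more patients entering after a change than the other, the relative risk (RR) would include a reform effect. None of the listed covariates would remove it: time since diagnosis measures an interval, and two patients with the same interval can enter on either side of July 2014.

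Several features leave room for unequal timing. Intake is open-ended. Recruitment by consent is described only for the intervention group. Control municipalities had still to be chosen, by their 2013 RTW rates and with compromise possible to reach the numbers (Methodological considerations).

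**Working it through.** **The plan's own accrual figure.** From Sample size calculation: 450 referrals a year, 20 % in the intervention municipalities, 80 % employed, 80 % consenting.

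- 450 × 0.8 × 0.8 = 288 a year, both groups together, as stated.
- 430 / 288 = 1.49 years, which reproduces the stated 1.5 years.
- 288 × 1.5 × 0.2 = 86 intervention patients, near the stated 90.

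The 1.5 years follows only if both groups fill together from one referral stream.

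**Speed of each group, with those factors.**

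- Intervention: 450 × 0.2 × 0.8 × 0.8 = 57.6 a year; 90 / 57.6 × 12 = 18.75 months.
- Control: 450 × 0.8 × 0.8 × 0.8 = 230.4 a year; (430 − 90) / 230.4 × 12 = 17.71 months.

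**Variant: controls need no consent (assumption).** 450 × 0.8 × 0.8 = 288 controls a year; 340 / 288 × 12 = 14.17 months.

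**Bias under a null intervention.** The difference in RTW equals the reform effect multiplied by the difference between groups in the share entering after the change. The control rate of 60 % is the article's. It gives no reform effect, so 3 and 10 points are assumed. Both groups are assumed to start in December 2013 and accrue evenly. December 2013 to June 2014 is 7 months.

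| Scenario | Included before July 2014 (intervention / control) | Gap | Null RR, 60 → 63 % | Null RR, 60 → 70 % |
|---|---|---|---|---|
| Article's factors | 7/18.75 = 37.3 % / 7/17.71 = 39.5 % | 2.2 points | 61.88/61.81 = 1.001 | 66.27/66.05 = 1.003 |
| No consent for controls | 37.3 % / 7/14.17 = 49.4 % | 12.1 points | 61.88/61.52 = 1.006 | 66.27/65.06 = 1.019 |

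**Moving the clock to end of treatment.** The shares above count inclusion, but follow-up starts later. In the no-consent variant, with a 10-point reform effect and an assumed treatment length:

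- 3 months: 4/18.75 = 21.3 % against 4/14.17 = 28.2 %; null RR 67.87/67.18 = 1.010.
- 6 months: 1/18.75 = 5.3 % against 1/14.17 = 7.1 %; null RR 69.47/69.29 = 1.002.

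**January 2015 instead of July 2014.** This is 13 months in, so the lag pushes less of it out of range. Attaching the same assumed 10 points to this date alone:

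- Article's factors, at inclusion: 13/18.75 = 69.3 % against 13/17.71 = 73.4 %; null RR 63.07/62.66 = 1.006.
- No consent, at inclusion: 69.3 % against 13/14.17 = 91.8 %, a 22-point gap; null RR 63.07/60.82 = 1.037.
- No consent, 6-month treatment: 37.3 % against 49.4 %; null RR 1.019.

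**Reference points.** If both groups have the same calendar distribution, the bias is zero whatever the reform did. The planned contrast is 82 % against 60 %, an RR of 82/60 = 1.37.

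**The case against.** The strongest reply is that a national reform reaches both groups and cannot bias a concurrent comparison. The sample size section treats the groups as concurrent. This stands, and it rules out several stronger readings.

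- A reader might infer that the planned contrast already mixes intervention and reform. The documents do not support that: it would need a difference in calendar distribution, or in local implementation, that they do not show.
- A reader might infer that the article's supply figures make the groups fill at different speeds. They do not. With its own factors the two times are 18.75 and 17.71 months. A wide gap appears only if the consent factor is dropped for controls, and on this the article is ambiguous: the sample size section applies consent to everyone, Ethical considerations says all patients consented, and the recruitment section describes consent for the intervention group alone.
- The warning of a longer inclusion period might be read as stretching one group only. It concerns the total number of survivors needed, so it gives no ground for that.
- The four-weekly interviews might be taken as introduced by the reform. The article says only that the law requires them.

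The population also weakens the mechanism. The limit may be lifted in cancer, and patients are often spared job-centre meetings during treatment. Against that, the Background and Discussion still treat the benefit limit, and loss of income while sick-listed, as relevant to these patients.

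Nor does the reform split follow-up evenly. With 18 months of even accrual and assumed treatment lengths of 0, 3 and 6 months, 89 %, 96 % and 99.8 % of maximum follow-up falls after July 2014. Averaging over two versions of usual care is therefore mainly a matter of interpretation and generalisability.

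Finally, a condensed article may leave record-search dates to the full protocol. That is fair for the dates. The covariate list, however, is printed and has no calendar term.

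**Conclusion.** The point holds as a modest gap, not as a demonstrated bias. The law changed during intake, the endpoint is read from benefit payments, and neither the control definition nor the adjustment list protects against unequal calendar timing.

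On the article's own factors the null RR is about 1.003 at July 2014. Without consent for controls it is about 1.02 counted at inclusion, and less at that date once entry is counted from end of treatment. January 2015 could contribute up to about 1.04 in the no-consent case. All these figures rest on an assumed 10-point reform effect, even accrual and a common start; a 3-point effect brings the July figures to 1.001 and 1.006. The cancer exception may make the true effect smaller. Against a planned RR of 1.37 the size is small. The change is still worth making, because this source of confounding in a non-randomised comparison can be closed with dates already held.

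**What to change.** 1. **Participants, Control group:** state that controls are drawn from the same calendar inclusion window as the intervention group, using the same anchoring event in the hospital records.
2. **Statistical analyses, Primary outcome:** add calendar period of entry to the adjusted primary model, with entry taken at end of treatment: before July 2014, July to December 2014, and from January 2015. Merge sparse periods. With a six-month treatment length (assumed), only about 90 × 1/18.75 ≈ 5 intervention patients would enter before July 2014.
3. Any RR by period should be labelled descriptive.

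The cost is one sentence and one covariate with at most two degrees of freedom. Treatment dates are in the hospital records and DREAM is weekly, so no new data are needed. The downsides are a slight loss of precision and possibly a smaller control pool. The sample size does not change.
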